## Abstract

*Aedes* and *Culex* mosquitoes, known for spreading arboviruses like dengue and West Nile, thrive in cities, posing health risks to urban populations. Climate change can create suitable climatic conditions for these vectors to spread further in Europe. Cities contain numerous landscape and infrastructure elements, such as storm drains, that allow stagnant water build-up facilitating mosquito breeding. Modifying urban infrastructure to prevent water accumulation can reduce mosquito populations, but evidence is limited. The Public Health Agency of Barcelona, Spain, introduced a structural modification of storm drains to prevent water accumulation. Together with the Agency, we designed a randomised controlled trial (RCT) to experimentally assess the effectiveness of these modifications on adult *Aedes albopictus* and *Culex pipiens* populations. It is a parallel-arm RCT with equal randomization of 44 drains to receive mosquito-proofing modifications (intervention) or not (control). Primary outcomes are adult mosquito counts and secondary outcomes are larvae and mosquito presence, assessed weekly at each drain until no mosquitoes are detected. Data analyses include generalised linear mixed models to estimate the time-averaged and highest intervention effects, subgroup and sensitivity analyses. The trial results will guide a city-wide expansion of the storm drain modifications and provide valuable evidence to enhance existing vector control measures.

Specifications table

**Table utbl0001:** 

Subject area:	Environmental Science
More specific subject area:	Public health, mosquito control, urban design, urban climate change adaptation
Name of your protocol:	The effectiveness of mosquito-proof storm drains on adult mosquito and mosquito larvae abundance: protocol of the IDAlErt storm drAin randomiSed controlled trial (IDEAS) in Barcelona, Spain
Reagents/tools:	Entomological aspirator: Improved Prokopack Aspirator Model 1419 from John W. Hock Co., powered by a 12 v 9.0 Ah valve-regulated, rechargeable sealed lead battery.
Experimental design:	This is a protocol for a randomised controlled trial (RCT) to investigate the effects of mosquito-proofing storm drains in Barcelona on the counts of adult *Aedes albopictus* and *Culex pipiens* mosquitoes. Using a parallel-arm design, we randomise 44 drains to receive mosquito-proofing modification (intervention) or not (control). The primary outcome is the combined counts of total adult *Ae. albopictus* and *Cx. pipiens* mosquitoes captured using an entomological aspirator during the trial period. Secondary outcomes include the presence of either mosquito larvae or adult mosquitoes (binary). The measurement of primary and secondary outcome takes place weekly until no mosquitos are detected. The effects of the intervention are estimated comparing mosquito-proofed and control drains using generalised linear mixed models.
Trial registration:	This trial is registered as a trial in Open Science Framework Registry. Registration DOI https://doi.org/10.17605/OSF.IO/JZQAH
Ethics:	The IDEAS trial does not involve human subjects and does not pose any significant health risks to the community. We leveraged the existing program for storm drain modifications by the ASPB and assigned the intervention by randomly selecting drains from a pool of storm drains eligible for modification. To date, no cases of locally transmitted mosquito-borne diseases affecting humans have been reported in the city of Barcelona, but the ASPB applies existing surveillance protocols for mosquito-borne arboviruses, including the necessary anti-larval and/or adulticide treatments if a human case is detected. Any such instances that affect drains included in the trial will be accounted for in the analysis. The trial does not include experiments with animals.
Value of the Protocol:	1. This protocol describes in detail the aims and methods of a randomized control trial designed together with a governmental public health agency to evaluate the effects of an urban infrastructure intervention on *Aedes albopictus* and *Culex pipiens* mosquito counts. 2. This study exemplifies a transdisciplinary collaboration between governmental stakeholders and universities to co-produce robust evidence to inform decision-making regarding the upscale of the intervention. 3. This trial will investigate an urban infrastructural intervention that potentially has far reaching implications in safe-guarding public health against mosquito-borne diseases and can be considered as an upstream prevention measure.

## Background

Cities are becoming increasingly vulnerable to vector-borne diseases (VBD) due to climate change [1,2]. Mosquitoes belonging to the *Aedes* and *Culex* genera, known carriers of arboviruses such as yellow fever, Zika, chikungunya, West Nile, and dengue viruses, are sensitive to climate, including temperature, humidity, and precipitation [3]. *Aedes* and *Culex* species are well adapted to human settlements, utilising stagnant water bodies for egg-laying and larval development [[4], [5], [6]]. Urban sewage systems with stagnant water or poor drainage propagate the breeding and proliferation of *Aedes* and *Culex* mosquitoes [7,8], creating opportunities for mosquitoes to lay eggs and complete their life cycle [8].

Mosquito vectors, including the *Culex pipiens* [4] and *Aedes albopictus* [9,10] species, present health risks throughout Europe. *Cx. pipiens* is native to the continent; *Ae. albopictus* is currently established in Europe's Mediterranean countries, Switzerland, Germany, Hungary, Romania, Moldova, Bulgaria, Serbia, Kosovo, Macedonia, Ukraine, Russia, Georgia, and Armenia [11]. In Spain, *Ae. albopictus* was first detected in 2004 near Barcelona [12] and has spread into eastern and northern provinces and farther inland [[13], [14], [15],^11^]. Despite active monitoring and control efforts, mosquito populations continue to proliferate. Changes in climate coupled with the availability of new ecological niches and immunologically naïve populations [1,16] pose challenges in controlling vector and pathogen spread. Adaptive strategies, including modifying urban infrastructure, can co-beneficially act as upstream preventative interventions against VBDs by affecting vector populations. Infrastructural modification can be costly, and, therefore, require causal evidence of their effectiveness before implementation and scaling.

Barcelona is a Mediterranean city with 1.7 million inhabitants, in which *Ae. albopictus* and *Cx. pipiens* populations are primarily managed through applying biocides in breeding sites [17,6]. In 2018, a dengue outbreak was detected in Barcelona, originating from the arrival of a viremic passenger into an area of *Ae. albopictus* activity [18]. This revealed that ongoing surveillance and control measures were insufficient for long-term reduction in breeding sites. Recognising the need for a paradigm shift, the Barcelona Public Health Agency (ASPB) began piloting an infrastructural modification to storm drains–‘mosquito-proofing’–that diverts stormwater into sewers rather than filtering it through the sand. Mosquito-proofing storm drains in urban public areas can: (i) minimise the establishment of breeding sites to future-proof the arrival of vectors [17], (ii) sever mosquito proliferation at existing breeding sites, and (iii) reduce the need for traditional biocide treatment in high-mosquito-activity drains [19].

Preliminary observations of mosquito-proofing storm drains in Barcelona show reduced mosquito larvae activity, reduced drain flooding and decreased reliance on biocide treatment [17]. Although initial results are promising, we require evidence from robust causal impact evaluations for widespread implementation of mosquito-proof storm drains. We are therefore conducting a randomised controlled trial (RCT) to investigate the effect of mosquito-proofing storm drain modifications on *Ae. albopictus* and *Cx. pipiens* abundance in Barcelona. RCTs provide a gold standard for causal inference evaluation and allow the observed effects to be attributable to the intervention [20]. This RCT will overcome the limits of the previous observational study, provide robust evidence of the effects of the storm drain modifications on the mosquito numbers in Barcelona, and support decision-making by the city government regarding a widescale implementation of the modification.

## Description of protocol

### Objectives

This protocol describes the aims and the methods of the IDAlErt storm drAin randomiSed controlled trial (IDEAS) in Barcelona, Spain. In the IDEAS trial, we aim to investigate the effect of urban mosquito-proofing storm drain modifications on *Ae. albopictus* and *Cx. pipiens* numbers found in these breeding sites. We hypothesise that modified storm drains will exhibit lower adult and larval mosquito abundance than unmodified drains. Whereas the observational study by Montalvo et al. [17] shows that drain modification reduces water accumulation and mosquito larval activity within the modified drains, it could be confounded by uncontrolled factors. Our study, thus, aims to ascertain the effectiveness of this infrastructure intervention within an experimental study that addresses the confounding factors. Our findings will add evidence to guide recommendations for implementing this intervention and strengthen vector control efforts.

This study is part of the larger Horizon Europe project “Infectious Disease decision-support tools and Alert systems (IDAlert)” (https://idalertproject.eu/). The IDAlert project aims to develop long-lasting solutions to reduce climate change-induced infectious disease risks through collaborations between multiple research institutes and decision-making stakeholders [21]. This trial involves direct collaboration between the Barcelona Public Health Agency (Agència de Salut Pública de Barcelona, ASPB), Universitat Pompeu Fabra (UPF), and Heidelberg University (UKHD). Ultimately, the evidence generated from this trial will inform decision-making regarding expanding storm drain modifications as a sustainable tool for VBD prevention.

### Trial design

IDEAS trial is a causal evaluation of a structural modification of urban storm drains envisioned by the Barcelona city administration to address mosquito-related threats and nuisances. We leverage the planned implementation to conduct a robust experimental study. Together with the governmental stakeholders, we designed a trial outlined in this protocol. We conduct a parallel-arm randomised controlled trial where eligible storm drains are randomised 1:1 to receive the mosquito-proofing intervention (intervention arm) or not (control arm). We selected eligible drains based on the detection of mosquito activity in 2022/2023 by the Barcelona Public Health Agency. We created a 200-meter zone around each eligible drain to account for mosquito dispersal capacity [[22], [23], [24], [25]] and minimise the risk of contamination across trial arms. We will measure outcomes in the intervention and control storm drains and in water bodies in the vicinity of the drains to capture mosquitoes that may be flying to experimental drains from nearby breeding sites. The overall design is illustrated in Fig. 1.

**Fig. 1 fig0001:**
[figure not shown]
The flow chart of the IDAlErt storm drAin randomiSed controlled trial (IDEAS) in Barcelona, Spain.

### Study setting

We are conducting the IDEAS trial from 26 June 2023 until no mosquitoes are detected in 2023, capturing the mosquito season in Barcelona, Spain. The intervention is implemented by ASPB and the Barcelona Cicle de l'Aigua (BCASA)–the city's water infrastructure authority. All storm drains included in this trial are located in the city's public spaces. The trial does not involve private property.

### Eligibility criteria

We defined two eligibility criteria for including storm drains in the IDEAS trial based on ASPB's mosquito surveillance and control program (Fig. 2). We first selected storm drains in which mosquito activity was detected during 2022. The sample of participating drains was augmented by selecting drains in which potential activity–defined as the accumulation of standing water–was detected from January to March 2023. We also required that selected drains must be at least 200 m from one another. Selection details are given in S1 File (Section: Allocation of intervention and concealment mechanism).

**Fig. 2 fig0002:**
[figure not shown]
The red dots depict the location of storm drains eligible for sampling based on activity. The yellow rings encompassing the red dots represent the drains (*n* = 44) we selected for IDEAS. The source of the base map in grey is from “Ground uses of the city of Barcelona”, CC BY 4.0, Ajuntament de Barcelona, 2016, available at https://opendata-ajuntament.barcelona.cat/data/en/dataset/mapa-usos-sol-wms).

### Interventions

Our intervention, i.e., mosquito-proofing modification of storm drains, is implemented by our partners at the Barcelona water infrastructure authority, BCASA. We first place honeycomb bricks at the base of the drain to provide structural integrity and subsequently added concrete to create a gradient. We connect the lowest point of the gradient to the discharge pipe, enabling the water to flow down the gradient to prevent water accumulation (Fig. 3). This rapid and low-cost mosquito-proofing intervention is intended to eliminate stagnant water in the catchment drain, rendering the drain unsuitable for mosquito reproduction.

**Fig. 3 fig0003:**
[figure not shown]
Panel a) depicts an unmodified storm drain with stagnant water, and panel b) depicts a modified storm drain. Source: We obtained photos from [17] with permission for re-use.

We did not modify the 22 storm drains in the control arm, which served as mosquito breeding sites. We do not apply larvicides to either the treatment or control drains during this trial unless there is a confirmed arbovirus case detected in proximity to the drain(s). In such circumstances, ASPB will activate standard treatment protocols for protecting public health [26]. ASPB is following existing treatment protocols for all non-participating drains.

### Criteria for excluding or modifying allocated interventions

Upon inspection, our partners at ASPB and the water infrastructure authority excluded drains that did not fit the inclusion criteria. We applied three exclusion criteria for selecting storm drains in our trial: (i) previously modified drains that were unreported in the public record, (ii) inaccessible drains in construction areas or where obstructed by public infrastructure, and (iii) obstruction from cars parked on top of the drains.

### Outcomes

Our objective in this trial is to assess the impact of storm drain modifications on *Ae. albopictus* and *Cx. pipiens* mosquito numbers inside intervention and control drains. Our primary outcome is the combined total counts of adult *Ae. albopictus* and Cx. *pipiens* mosquitoes sampled at each drain. The secondary outcome is drain activity defined as the presence of either adult mosquitoes or *Ae. albopictus* and *Cx. pipiens* larvae (L1-L2, L3-L4, and pupae stages) in drain water inside the drains. We sample water elements to collect adult mosquitoes and larvae at these alternative breeding sites. We also measured the depth of water (cm) in corresponding drains. One trained ASPB technician measures the primary and secondary outcomes starting on 26 June 2023 and continuing until no mosquitos are detected, visiting each participating drain once per week.

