### Larval sampling

Our technician collects a water sample from the drain to assess the presence of mosquito larvae. After submerging the dipping tool (volume 0.5 L with a 1.5-meter long handle) vertically into the water, our technician withdraws the dipping tool to pour the water sample into a designated container [17]. Using pipettes, our technician individually extracts larvae and transfers them into vials. When the water level is low and predominantly contains organic matter such as dirt and debris, we use a hand collector to gather the larvae. We send the vials to the laboratory for species determination. If possible, our technician approximates the number of larvae in the drain stratified by larvae development stages (i) L1-L2 stages, and (ii) L3-L4 stages, and (iii) pupae.

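### Larvae are in the title and hypothesis, but the secondary outcome as defined pools them with adults and does not isolate the larval effect

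*Protocol article*

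**What the plan says.** The protocol name in the specifications table is "The effectiveness of mosquito-proof storm drains on adult mosquito and mosquito larvae abundance". The Objectives section carries both parts into the hypothesis: "We hypothesise that modified storm drains will exhibit lower adult and larval mosquito abundance than unmodified drains".

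The outcomes are narrower. The Outcomes section says "Our primary outcome is the combined total counts of adult" mosquitoes of the two species. It then gives one secondary outcome, in the singular: "The secondary outcome is drain activity defined as the presence of either adult mosquitoes or" larvae or pupae of those species in the drain water. The specifications table also pools the two: "Secondary outcomes include the presence of either mosquito larvae or adult mosquitoes (binary"). The abstract reads differently: "secondary outcomes are larvae and mosquito presence, assessed weekly at each drain". That could mean one outcome or two.

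The Statistical methods section breaks down adult counts by species, sex and month. It names no larvae-only outcome or model. Larvae are nevertheless collected separately. The Larval sampling section describes dipping for larvae and sending them for species identification, and adds: "If possible, our technician approximates the number of larvae in the drain stratified by larvae development stages".

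**The concern.** The modification is meant to stop breeding by removing standing water (Interventions section), so larvae are the most direct measure of whether it works. Adults are less specific: the Trial design section accepts that adults caught at a trial drain may have flown in from breeding sites nearby.

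Under the either/or definition, one target-species adult makes the visit positive. Larvae can change the outcome only at visits where no adult is caught. The secondary outcome is therefore close to a yes/no version of the primary outcome. If the plan is followed as written, the larval part of the hypothesis has no outcome of its own. A reader could then take a composite result as evidence about breeding, in either direction, when it need not be. This matters because the results are meant to guide a city-wide expansion.

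**Working it through.** **Plan's own figure.** The article gives no effect size or power for the secondary outcome. Its stated power of at least 90% for a 35% difference with 44 drains concerns adult counts, and this point does not rest on it.

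**Inputs.** The either/or rule comes from the Outcomes section. The article gives no prevalence of adults or larvae per visit, so every prevalence below is an assumption chosen for illustration.

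**Formula.** Let *a* be the probability that adults are present at a visit and *l* the probability that larvae or pupae are present. If the two are independent, P(composite) = 1 − (1 − *a*)(1 − *l*).

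**Case 1: larvae fall, adults do not.** Larvae 30% control, 5% modified; adults 50% in both arms.
- Control: 1 − 0.50 × 0.70 = 65.0%. Modified: 1 − 0.50 × 0.95 = 52.5%. Difference 12.5 points, against 25 for larvae alone.
- Odds ratio (control to modified): composite (0.65/0.35)/(0.525/0.475) = 1.7; larvae alone (0.30/0.70)/(0.05/0.95) = 8.1.

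**Case 2: larvae and adults both fall.** Larvae as before; adults 50% control and 50% × 0.65 = 32.5% modified. This applies the planned 35% reduction in counts to presence, which is itself an assumption.
- Control: 65.0%. Modified: 1 − 0.675 × 0.95 = 35.9%. Difference 29.1 points, more than the larval 25.
- Odds ratio: (0.65/0.35)/(0.359/0.641) = 3.3.

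**Case 3: adults fall, larvae do not.** Larvae 10% in both arms; adults 60% versus 20%.
- Control: 1 − 0.40 × 0.90 = 64%. Modified: 1 − 0.80 × 0.90 = 28%. Difference 36 points, with a larval difference of zero.

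**Range over dependence.** Independence is doubtful, because adults may emerge from the drain's own larvae. The extremes are full overlap, P = max(*a*, *l*), and no overlap, P = *a* + *l*.

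| Case | Larval difference | Composite, full overlap | Composite, independent | Composite, no overlap |
|---|---|---|---|---|
| 1 | 25 | 50 − 50 = 0 | 12.5 | 80 − 55 = 25 |
| 2 | 25 | 50 − 32.5 = 17.5 | 29.1 | 80 − 37.5 = 42.5 |
| 3 | 0 | 60 − 20 = 40 | 36 | 70 − 30 = 40 |

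**Range over adult prevalence.** If *a* is equal in both arms and independent of larvae, the composite difference is (1 − *a*) times the larval difference. A 40-point larval difference (50% versus 10%) becomes 32, 24, 16 or 8 points as *a* rises through 20%, 40%, 60% and 80%.

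The same larval effect can thus give a composite difference that is smaller or larger than the larval one, and a large composite difference can occur with no larval effect.

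**The case against.** Three objections carry weight.

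*A larval analysis may exist elsewhere.* The abstract uses the plural and the table says that secondary outcomes include the composite. Supplementary material and any SAP are not shown, and reporting the components of a composite is often left to such documents. A reader might infer that the larval effect will never be tested, or that the trial cannot say whether breeding stops. The article does not support that: the data are collected, and an analysis may be planned outside this document. What stands is that the Outcomes section fixes a definition that pools the two, and no part of the article defines a larval outcome.

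*The composite need not dilute.* A reader might infer from Case 1 that half the effect is lost. That result requires no effect on adult presence, contrary to the trial's own hypothesis, together with independence. Case 2 removes the first assumption and the difference exceeds the larval one. The objection holds against any single figure for the loss. It does not rescue the composite, because a difference inflated by adults is no better evidence about larvae than a diluted one.

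*The design deals with fly-in, and drain activity is a sensible concept.* Trial drains are at least 200 m apart, nearby water features are sampled, and mosquito activity was also used for eligibility. These are reasons to keep the composite. They do not let it separate larvae from adults.

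Two limits on the remedy also stand. Larval presence does not test larval abundance. And if the modification works as intended, the modified arm may have no larval events, in which case an ordinary logistic mixed model gives no finite odds ratio.

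**Conclusion.** The point holds as a poorly chosen definition and a misalignment within the article: larvae are part of the stated question, but the defined outcomes do not measure them separately. The overlap with the primary outcome follows from the definition and needs no assumption.

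The numerical distortion has no single size. In the illustrations, a 25-point larval difference appears as 12.5 or about 29 points under independence, and as anything from 0 to 42.5 points across the dependence extremes. A zero larval difference appears as 36 to 40 points. All of this rests on assumed prevalences.

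The change is worth making, but the defect is confined to the secondary outcome. The primary adult-count comparison and its power calculation are untouched.

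**What to change.** - Define larval or pupal presence per visit (any of L1-L2, L3-L4 or pupae of the two species) as its own secondary outcome. Keep the adult-or-larva composite as supportive. Use the same wording in the abstract, the specifications table and the Outcomes section.
- Code a drain that was inspected and found dry as larvae absent, not missing. Larvae are sampled from water and the intervention removes water, so treating dry drains as missing would discard the visits at which it worked. Presence and depth of water are already recorded.
- Analyse the outcome with a binary mixed model with a random effect for drain. Specify in advance a penalised model or an exact drain-level comparison if the modified arm has few or no events.
- State that larval abundance is assessed as presence, with the approximate stage-specific numbers reported descriptively, since they are recorded only where feasible.

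The cost is one extra secondary model with its sparse-data fallback. No fieldwork is added, because larvae are already sampled at the weekly visits and identified in the laboratory.
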